## Abstract

**Background:**

Chronic pain imposes a substantial burden on individuals and society. Cognitive behavioral therapy for chronic pain (CBT-CP) has proven effective internationally, but randomized evidence in Japan is scarce. The first Japanese trial was a single-center, 16-session videoconference program that prioritized pain intensity. In contrast, this multicenter trial tests a brief, face-to-face, individualized CBT-CP program with quality of life (QoL) as the primary outcome.

**Methods:**

This open-label, randomized, parallel-group superiority trial enrolls 60 adults aged 20–80 years with chronic pain persisting ≥ 3 months and EQ-5D-5L scores ≤ 0.80, indicating reduced QoL. Participants are randomized 1:1 to treatment as usual (TAU) plus an eight-session CBT-CP program or to a waitlist control receiving TAU only. The manualized intervention includes psycho-education, relaxation, activity pacing, and cognitive restructuring, delivered weekly face-to-face, with the goal of completing eight sessions within 14 weeks. If necessary, sessions may extend beyond the 15th week; however, the post-assessment is always conducted at 15 ± 2 weeks irrespective of intervention timing. Therapists meet prespecified eligibility criteria and receive structured training, supervision, and fidelity monitoring. The primary outcome is QoL (EQ-5D-5L) at 15 ± 2 weeks. Secondary outcomes include pain intensity, disability, depressive symptoms, catastrophizing, fear of movement, pain self-efficacy, and health-related QoL assessed by the SF-12. These outcomes, together with prognostic risk and somatic symptom burden, will also be examined as potential mediators or moderators. The intervention group undergoes a 27 ± 2-week follow-up to explore mid-term durability in a single-arm pre/post analysis. Analyses follow the intent-to-treat principle using linear mixed models, with effect sizes and confidence intervals reported; multiplicity will be considered in interpreting secondary outcomes. Blinding of participants and therapists is not feasible.

**Discussion:**

This trial will clarify the added value of a brief, fidelity-assured, face-to-face CBT-CP program in Japan, where implementation remains limited. Findings are expected to guide clinical adoption, workforce training, and dissemination, while also generating hypotheses about for whom and through which processes CBT-CP may confer benefit.

**Trial registration:**

University Hospital Medical Information Network Clinical Trials Registry, UMIN000042798. Registered on 21 December 2020, https://center6.umin.ac.jp/cgi-open-bin/ctr_e/ctr_view.cgi?recptno=R000048858.

## Introduction

### Background and rationale {6a}

Chronic pain typically lasts more than 3 months [1, 2] and is defined as “an unpleasant sensory and emotional experience associated with, or resembling that associated with, actual or potential tissue damage” [3]. Chronic pain causes various problems, including behavioral problems owing to decreased activities of daily living (ADL) [4], emotional problems such as depression and/or anxiety [5], cognitive problems such as catastrophizing [6], and general problems such as decreased quality of life (QoL) [7, 8]. The prevalence of chronic pain is 11–40% in the USA [9], 35–51% in the UK [10], and 13–26% in Japan [11]. The annual loss of social productivity due to chronic pain is estimated to be $560–635 billion in the US [12] and $19.9 billion in Japan [8]. Thus, it has an enormous impact on individuals and society, and managing it is an important issue.

The ultimate goal of chronic pain treatment is not to attain pain-free conditions but to manage the pain to improve QoL and/or ADL [13, 14]. Cognitive behavioral therapy (CBT) is a psychological approach to managing the psychosocial factors that interact with chronic pain, and many clinical trials have demonstrated its efficacy and cost-effectiveness for chronic pain. A Cochrane Collaboration systematic review found that CBT for chronic pain (CBT-CP) significantly reduced pain intensity, disability, and distress compared to standard treatment (standardized mean difference (SMD) = − 0.22, − 0.32, − 0.34) in adult patients and maintained the effects for several months (SMD = − 0.16, − 0.21, − 0.25) [15]. In a randomized controlled trial (RCT) of CBT-CP in patients with subacute and chronic low back pain, those who received CBT-CP experienced reduced pain and improved ADL and QoL after 12 months, and their treatment costs were half to one-fifth of those undergoing acupuncture, exercise therapy, or manual therapy [16]. Consequently, CBT-CP has often been described as the gold standard psychological approach for individuals with different pain problems [17].

In Japan, although CBT-CP has been recommended in various Japanese guidelines based on evidence from Western studies, its validation has been delayed and its prevalence remains limited [14]. Only a small number of clinical trials on CBT-CP have included Japanese participants, mainly consisting of retrospective studies comparing responders and non-responders to treatment with insufficient assurance of therapist quality [18, 19]; a practice report of exercise therapy combined with psycho-education of CBT with a self-administered text [20]; and a few single-arm, pre/post studies without control groups [21–23]. Reflecting this lack of research, in medical practice in Japan, about 70% of treatments are massage, medication, and physical therapy; about 25% are acupuncture, prosthesis therapy, block therapy, and surgery; and about 4–7% fall into other categories, only a portion of which are psychological approaches, typically delivered by psychologists, including CBT-CP [24, 25]. This overall insufficiency in both research and practice is underscored by the latest Japanese guideline (2021), which explicitly states that although the implementation of CBT-CP can be recommended, a suitable environment, including the availability of trained psychologists, is not yet in place and the implementation system in Japan requires prompt development [14]. Subsequently, the first RCT of CBT-CP in Japan was reported in 2021 [26]. However, it was performed as a single-center study with a small sample size of 30 patients, and the primary outcome was pain itself, rather than QoL, considered the highest priority [13, 14]. In addition, although the RCT employed a 16-session program that included many modalities to be applicable to a wide range of patients, it is also important to develop a short-term program with selected modalities and to examine its efficacy, as a shorter program would be more acceptable in medical practice in Japan. To enhance the generalizability of CBT-CP in Japan, developing short-term CBT-CP programs and, in particular, rigorously testing them in large-scale multicenter trials with QoL as the primary outcome will be essential steps. Alongside this primary focus on QoL, secondary outcomes will include a range of psychosocial variables (e.g., pain severity, disability, and mental health), allowing assessment of broader effects of CBT-CP on patients’ functioning and well-being. In addition, assessing mid-term outcomes at follow-up will provide insights into whether treatment effects are sustained beyond the immediate post-intervention period.

Previous reviews have highlighted that the mechanisms of change in CBT remain insufficiently understood and that carefully designed studies are needed to clarify the role of potential mediators and moderators [27]. In this context, exploratory analyses of such variables may provide useful insights, particularly when QoL is the primary outcome. In this trial, however, these analyses remain exploratory, while the primary objective is to establish whether CBT-CP can improve QoL in Japanese patients.

Additionally, to rigorously evaluate the efficacy of CBT-CP, it is essential that interventions are appropriately conducted. Some previous clinical trials noted insufficient assurance in this regard [15]. Therefore, it is necessary to clearly indicate how therapists were trained in advance and to monitor whether the content of CBT-CP delivered is appropriate and whether the therapeutic process is adequate. Ensuring these procedures and treatment fidelity is a prerequisite for verifying the efficacy of CBT-CP, while also providing a reliable foundation for subsequent exploratory analyses of its mechanisms.

No formal patient or public involvement was implemented in the design, conduct, or reporting of this trial. However, the trial was designed with a primary focus on patient-reported outcomes, and experiences from the preceding pilot study with Japanese patients informed the refinement of the program and trial procedures.

### Objectives {7}

The primary objective of this multicenter RCT is to examine whether an eight-session individualized CBT-CP program, in addition to treatment as usual (TAU), improves QoL in Japanese patients with chronic pain compared with a waitlist control group receiving TAU only. The primary outcome is QoL, assessed using the EuroQol five-dimensional questionnaire five-level (EQ-5D-5L), measured at baseline and at 15 ± 2 weeks.

Secondary objectives are to evaluate the effects of CBT-CP on related psychosocial factors, and to assess mid-term effects in a single-arm pre/post comparison at 27 ± 2 weeks.

Exploratory objectives are to examine whether psychosocial variables, participant characteristics, and process measures function as potential mediators or moderators of treatment response.

### Trial design {8}

The study uses a multicenter, open-label, randomized, parallel-group superiority design and will involve 60 patients aged 20–80 years with chronic pain. Initial evaluation is conducted after obtaining informed consent, and eligible patients undergo a baseline assessment within 4 weeks and are enrolled as participants. Participants are randomized in a 1:1 allocation ratio to the intervention group (TAU plus an eight-session CBT-CP program) or the waitlist control group (TAU only). Participants in the waitlist group continue their usual care without CBT-CP until the post-assessment at 15 ± 2 weeks after randomization, after which they are offered the intervention.

### Eligibility criteria {10}

#### Inclusion criteria (all must be met)

Chronic pain persisting for at least 3 monthsEQ-5D-5L ≤ 0.80Disability attributable to chronic painAge 20–80 yearsAble to understand the study and provide written informed consent

#### Exclusion criteria (any of the following)

Currently receiving other psychotherapy or participating in another clinical trialPrevious receipt of CBT for chronic painScheduled to receive medical examinations or treatments that may interfere with participation or outcomes, specifically: (1) interventional pain procedures such as surgeries, orthopedic procedures, nerve blocks, or trigger point injections; (2) prescription of medical narcotics, even if type and dosage are fixed; and (3) intravenous infusion for pain relief.Pain with an organic cause requiring immediate medical attentionChronic pain mainly consisting of headache (primary or secondary). Headache has traditionally been reviewed separately and is generally managed through distinct treatment pathways and outcome domains [15, 27], making its inclusion less consistent with the aims of this trial.Chronic pain due to surgery or external injuryCurrently receiving compensation or benefits related to litigation for chronic painAlcohol or substance use disorderManic episodes or any psychotic disorderSevere suicidal ideationCognitive impairment that precludes participation in CBTInsufficient ability to communicate, read, or write in JapanesePregnancyAny other condition deemed unsuitable by the attending physician

### Additional consent provisions for collection and use of participant data and biological specimens {26b}

No biological specimens are collected in this trial, and no incidental findings are expected. Regarding participant data, the consent procedure includes provisions for possible secondary use. Specifically, anonymized data obtained in this study may be used for ancillary analyses by the investigators or shared in public databases or with other researchers for purposes such as replication or meta-analysis. Any such use will require prior approval by the relevant institutional ethics committee, and only data that cannot identify individual participants will be shared.

## Interventions

### Explanation for the choice of comparators {6b}

The comparator in this trial is TAU only, corresponding to a waitlist control group. In both groups, participants continue their stable usual care (e.g., prescription medications or insurance-covered physical therapy) or receive no specific treatment, provided they do not meet the exclusion criteria. Treatments listed in the exclusion criteria, such as interventional procedures, medical narcotics, or intravenous infusions for pain relief, are not permitted as part of TAU. In Japan, there is no standardized definition of TAU for chronic pain in the Japanese clinical guidelines for chronic pain [14, 28]. These guidelines present graded recommendations for pharmacological, interventional, physical, and psychological treatments but do not specify a fixed package of “usual care.” Accordingly, TAU in this study is defined as the continuation of each participant’s ongoing treatment situation without initiating new interventions or changing the type, dosage, or administration of existing treatments. Participants in the intervention group receive CBT-CP in addition to TAU, while those in the control group remain on TAU only until the post-assessment at 15 ± 2 weeks after randomization. This approach is consistent with how TAU or waitlist control conditions have been treated in international trials and systematic reviews [15, 27].

### Intervention description {11a}

CBT-CP in this study is a structured and manualized eight-session program, with an original workbook and worksheet consisting of psycho-education, relaxation training, activity pacing, cognitive restructuring, and summary and relapse prevention (Table 1). Materials from the pilot version of the program have already been made freely available to healthcare professionals via the study website (in Japanese), and the present trial materials are planned to be published after study completion to support dissemination of CBT-CP in Japan. Participants will undergo eight sessions of CBT-CP, each lasting approximately 40 min, with the aim of completing the program within 14 weeks. If necessary, sessions may extend beyond the 15th week; however, the post-assessment is conducted at 15 ± 2 weeks irrespective of the intervention schedule. Homework will be provided in each session so that participants can practice the skills learned in real-life situations. The sessions are arranged face-to-face and weekly, unless inconvenient for the participant or therapist. If the therapist and participant cannot complete all the content in eight sessions and both deem it necessary, up to two additional sessions may be permitted.

**Table 1 Tab1:** Outline of the CBT-CP program

Session	Components	Homework
1	Psycho-education regarding CBT and chronic pain (CBT model, self-monitoring) and goal setting	Identifying vicious cycles using the CBT model
2	Relaxation training (breathing method, progressive muscle relaxation)	Practicing relaxation
3	Activity pacing 1 (reviewing the relationship between behavior and pain)	Recording activity log
4	Activity pacing 2 (setting the pace of activity and rest periods)	Practicing the set activity
5	Activity pacing 3 (adjusting the pace, including countermeasures against obstacles to activity)	Practicing activity including obstacle countermeasures
6	Cognitive restructuring 1 (identifying and distancing cognitive factors that interfere with activity)	Identifying obstructive cognition
7	Cognitive restructuring 2 (attempting to alter cognitive factors that interfere with activity)	Distancing from and restructuring the cognition
8	Summary and relapse prevention	Continuing to use the skills that have served them well

*Abbreviations: CBT-CP* cognitive behavioral therapy for chronic pain, *CBT* cognitive behavioral therapy

In Session 1, the therapists reiterate that the purpose of the CBT-CP program is not to attain pain-free conditions but to improve QoL. Subsequently, through self-monitoring, participants practice capturing the problems caused by chronic pain using the CBT model. The CBT model shows that humans respond to their circumstances, including situations and interpersonal relationships, in four aspects—cognitive, emotional, behavioral, and physiological—which all interact with each other. Finally, the participants discuss their individual goals and hopes for improvement through CBT-CP.

In Session 2, breathing and progressive muscle relaxation techniques are implemented to relax the body and mind and experience how autonomous and intentional activities can change the four aspects of the CBT model and their interactions.

In Sessions 3–5, activity pacing, the core intervention of our CBT-CP program, will be conducted. After reviewing the relationship between behavior and pain using an activity log, participants will choose their favorite activities that they value and set the pace of the activity and rest periods. In addition, obstacles to implementing these activities will be identified and countermeasures will be taken. Activity pacing could combine other behavior change techniques, such as behavioral activation and exposure [29], and can be tailored to the participant’s chosen or preferred activity.

In Sessions 6–7, the focus will be specifically on the cognitive factors that interfere with the activities undertaken in the previous sessions. The first goal is to be aware of the factors; then, to distance oneself from them, such as through externalization; and finally, to develop skills not influenced by the factors so that the activity initiated by participants in Sessions 3–5 is maintained.

In Session 8, participants summarize their learning from CBT-CP and discuss measures to prevent recurrence.

CBT-CP is to be conducted face-to-face but is allowed to be conducted remotely only if specified conditions are met. When it is inappropriate to provide CBT-CP face-to-face to comply with regulations by the government, local governments, and implementing institutions to prevent the spread of the novel coronavirus infection, online implementation is acceptable if the requirements based on the respective revised guidelines for the appropriate implementation of telemedicine and safety management of medical information systems in 2018 and 2017, by the Japanese Ministry of Health, Labour and Welfare, are met. This contingency applies only to such official regulations and not to individual-level infection risk. Online implementation is limited to the period during which the regulation is imposed, and face-to-face implementation will be resumed as soon as the regulation is lifted. In addition, it is permitted only if predefined requirements are met, such as approval from the attending physician, no recent history of requiring emergency face-to-face care, access to appropriate equipment and secure internet at the participant’s own expense, availability of a quiet private space, and the establishment of a safety plan in advance (e.g., emergency contacts and procedures).

### Criteria for discontinuing or modifying allocated interventions {11b}

Participants who meet any of the following discontinuation criteria will be excluded from the study:Declines to participate in the study or withdraws consentNo contact for more than 1 month. This is defined as failure to attend scheduled sessions and lack of response to repeated contact attempts (e.g., phone calls or study-related emails) from therapists or medical staff during that period.Difficulty in continuing the study owing to a serious adverse eventDid not meet the eligibility criteria at the enrollment stageThe entire study is terminatedThe principal investigator and research collaborators determine that it is appropriate to terminate participation in the study for other reasons

Notably, CBT-CP is designed to be completed within 14 weeks, but sessions may occasionally extend beyond the 15th week. Such extensions are not considered protocol violations, provided that the post-assessment is conducted at 15 ± 2 weeks.

If the Ethical Review Board recommends or directs discontinuation of the study, it will be terminated. Additionally, the principal investigator will consider whether to continue the study when any of the following events occur:Critical information is obtained regarding the quality, safety, or efficacy of the treatmentThe Ethical Review Board instructs the investigator to change the protocol and it is deemed difficult to accept the change

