### Plans to promote participant retention and complete follow-up {18b}

To promote retention, session schedules (timing and rescheduling) are arranged flexibly, and CBT-CP is provided face-to-face under ordinary circumstances. However, when sessions cannot be held in person owing to regulations by the government, local governments, or implementing institutions, online implementation is also permitted under predefined safety requirements (see Item 11a). Similarly, for the post-assessment and follow-up assessment, if participants are unable to attend within the assessment window, they may complete a mailed questionnaire or provide responses by telephone (see Item 13). Therapists also encourage engagement by reviewing and adjusting homework as appropriate, thereby supporting adherence throughout the intervention.

For participants who discontinue or withdraw from the study, outcome data are still collected at post-assessment, and at follow-up for the intervention group, whenever possible. All available data are included in the analysis according to the intent-to-treat (ITT) principle.

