## Statistical methods

### Statistical methods for primary and secondary outcomes {20a}

A detailed statistical analysis plan (SAP) will be developed and finalized prior to database lock.

The main analysis will estimate the effect size for the primary outcome (EQ-5D-5L) using LMM [64] based on the ITT principle. The LMM method is selected because of its strength in handling missing data and its ability to incorporate random effects. The analyses will be conducted with the outcome scores at each assessment time point as the dependent variable, time (baseline and post-assessment), group (intervention vs. waitlist control), and interaction between time and group as fixed effects, and participants as random effects. No special treatment will be applied to discontinued cases or missing values for ITT analysis, but as a sensitivity analysis, best- and worst-case scenarios will be examined by imputing hypothetical maximum and minimum plausible values based on the ranges of each scale, defined a priori and prespecified in the SAP. To address the potential non-normality and ceiling effects of the EQ-5D-5L, alternative modeling approaches (e.g., generalized linear models, beta regression) will also be considered in the SAP. Two-sided *p* values < 0.05 will be considered statistically significant.

Secondary analyses will estimate effect sizes for multiple psychosocial outcomes using the same LMM framework. In addition, the intervention group will undergo a follow-up assessment at 27 ± 2 weeks after randomization, and the mid-term effect of CBT-CP will be explored in a single-arm, pre/post comparison. Because multiple secondary outcomes (approximately 11 variables) will be analyzed, type I error will be controlled using Bonferroni correction. However, given the limited sample size, this conservative adjustment is expected to markedly reduce statistical power. Therefore, unadjusted results will be reported as the primary descriptive findings, while results with Bonferroni correction will also be presented to indicate the potential risk of type I error. Effect sizes and CI will be reported to aid interpretation, and all analyses of secondary outcomes will be considered exploratory and primarily hypothesis-generating.

Exploratory analyses will examine whether psychosocial variables, participant characteristics, and process measures function as potential moderators or mediators of treatment effects.

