### Methods in analysis to handle protocol non-adherence and any statistical methods to handle missing data {20c}

The primary analysis will follow the ITT principle. Protocol non-adherence will not lead to exclusion from the ITT set; per-protocol analyses are not planned. Missing outcome data will be handled within the LMM framework, and no special imputation is applied for the primary analysis. As sensitivity analyses, best-case and worst-case scenarios will be examined using hypothetical values defined a priori and prespecified in the SAP.

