## Oversight and monitoring

### Composition of the coordinating center and trial steering committee {5d}

The coordinating center for this trial is located at Kansai University, led by the principal investigator, who is responsible for overall trial management and day-to-day coordination. Although no independent trial office is established, the principal investigator directly oversees all organizational aspects of the study. In addition, a research assistant at the National Center of Neurology and Psychiatry assists with tasks related to the EDC system and data coordination.

Oversight of the trial is provided through a Trial Steering Committee convened every 2 months. Attendance is prioritized to ensure that the principal investigator and the site principal investigators (or, when necessary, a delegate from each site such as a therapist) are present. However, all trial team members are invited to participate, and attendance by additional investigators or therapists beyond the site principal investigators is welcomed. The committee reviews recruitment progress, enrollment numbers, reasons for discontinuation or dropout, adverse events, and data entry status, and also serves as the forum for discussing and, when necessary, adjudicating issues such as the interpretation of inclusion/exclusion criteria, given the heterogeneous clinical profiles of patients with chronic pain.

Day-to-day project management is conducted by the principal investigator at Kansai University, with technical support for the EDC system provided by the Translational Medical Center of the National Center of Neurology and Psychiatry. At each study site, the site principal investigator (a collaborating physician) holds ultimate responsibility for local trial conduct, including patient recruitment, informed consent, and adherence to protocol procedures.

No separate stakeholder or public involvement group has been established for this trial.

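### Section 11b excludes participants from the study on grounds that sections 18b, 20a and 20c treat as compatible with follow-up and ITT analysis, and randomised participants later found ineligible are not clearly covered

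*Protocol article*

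**What the plan says.** Section 11b of the protocol article introduces its list with "Participants who meet any of the following discontinuation criteria will be excluded from the study". There are six entries: declining or withdrawing consent, no contact for more than a month, difficulty continuing after a serious adverse event, not having met eligibility at enrolment, termination of the whole study, and a decision by the principal investigator and collaborators for other reasons. The no-contact entry is spelled out: "This is defined as failure to attend scheduled sessions and lack of response to repeated contact attempts". Both parts are required.

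Three other sections describe what happens to such people:

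- Section 18b: "For participants who discontinue or withdraw from the study, outcome data are still collected at post-assessment". The sentence goes on to include the later follow-up in the intervention arm, and it qualifies both with a statement that collection happens where possible. The next sentence reads "All available data are included in the analysis according to the intent-to-treat (ITT) principle".
- Section 20a: "No special treatment will be applied to discontinued cases or missing values for ITT analysis".
- Section 20c: "Protocol non-adherence will not lead to exclusion from the ITT set; per-protocol analyses are not planned".

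Two further sections bear on who applies the rule. Section 17a says that participants, physicians, therapists and the research assistant cannot be masked. Section 5d gives the Trial Steering Committee, when necessary, the task of "adjudicating issues such as the interpretation of inclusion/exclusion criteria".

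**The concern.** The heading of 11b is about discontinuing or modifying allocated interventions, but the only consequence its list gives is exclusion from the study. It does not separate three different events: stopping sessions, ending outcome collection, and leaving the analysis set. A site reading 11b alone could reasonably stop approaching a participant whom 18b says should still be assessed.

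Two features make this more than loose wording. First, the no-contact entry is defined through scheduled sessions, and before the post-assessment only the intervention arm has CBT-CP sessions, so controls cannot meet that definition in the same way. Second, the eligibility and discretionary entries are applied by people who know the allocation, with no independent data monitoring committee (21a) and no independent audit (23). What is at stake is week-15 EQ-5D-5L data that would be lost unevenly by arm, or randomised participants dropped after allocation is known.

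**Working it through.** The plan gives no figure for this point, so the check is mainly a comparison of texts.

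**Step 1: each 11b ground against the follow-up and analysis sections.**

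| Ground in 11b | Outcome collection (18b) | Analysis set (18b, 20a, 20c) |
|---|---|---|
| No contact for more than a month | Continues where possible | Stays in ITT; conflicts with exclusion |
| Serious adverse event, or investigator decision | Continues where possible, if read as discontinuing | Stays in ITT on the same reading; conflicts with exclusion |
| Did not meet eligibility at enrolment | Not named | Not named: 20c covers non-adherence, 18b those who discontinue or withdraw |
| Withdrawal of consent | 18b covers withdrawal from the study, where possible, but does not separate withdrawal from treatment from withdrawal from data collection | Available data analysed |

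The conflict is direct for the no-contact ground and least resolved for ineligibility.

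**Step 2: who can trigger the no-contact rule.** It needs missed sessions and no response to repeated contact attempts over more than a month. The comparator section (6b) and section 18a place CBT-CP for the waitlist arm after the post-assessment. Sessions in the intervention arm run over weeks 1–14 (Table 2), so the rule can take effect well before week 15. The other grounds can arise in either arm.

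**Step 3: why nominal ITT membership would not repair a lost outcome.** The primary model in 20a has two time points, with time, group and their interaction as fixed effects and participant as a random effect. Someone excluded in mid-treatment and not approached at week 15 contributes only a baseline score. Attendance is not in the model, so the intervention arm's post-assessment mean then rests on those who stayed, given baseline.

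**Step 4: illustration of size, on assumed values.** The documents give an anticipated effect of 0.74, a dropout of 20% not split by arm or reason, a correlation of 0.50, and 30 per arm. They give neither the rate of no contact nor the outcomes of those affected.

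- *Illustration A.* Assume that attenders gain 0.74 SD, non-attenders gain nothing, and k of 30 in the intervention arm drop out of the estimate. The effect with everyone counted is 0.74 × (30 − k)/30.
  - k = 3: 0.74 × 27/30 = 0.67, and 0.74/0.666 = 1.11 (+11%).
  - k = 6: 0.74 × 24/30 = 0.59, and 0.74/0.592 = 1.25 (+25%).
- *Illustration B.* Assume no treatment effect. A share x of the intervention arm is lost, and their outcomes are g SD worse than the rest. Bias = x × g.
  - Low end: 0.05 × 0.25 = 0.0125 SD, which is 2% of 0.74.
  - High end: 0.20 × 1.0 = 0.20 SD, which is 27% of 0.74.
  - Type I error at the high end: SE = √(1 − 0.50²) × √(1/30 + 1/24) = 0.866 × 0.274 = 0.237. The shift is 0.20/0.237 = 0.84 SE, which gives a two-sided error of about 0.135 against the nominal 0.05. At the low end it stays at about 0.05.

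Both illustrations require that the outcomes really are missing from the estimate.

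**The case against.** The strongest reply is that the analysis question is answered elsewhere. Section 11b mentions neither the analysis set nor deletion of data. Sections 18b, 20a and 20c keep discontinued participants in, and no per-protocol analysis is planned. This largely stands. A reader might infer that the plan removes poor attenders from the intervention arm's analysis. The documents do not say so, and 18b and 20c largely deny it.

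Other tempting readings also fail:

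- *Missed sessions alone lead to exclusion.* They do not. A poor attender who answers the telephone does not meet the definition. Someone who does meet it is hard to reach and may have no week-15 outcome under any wording.
- *The eligibility entry is a rule for removing randomised participants.* It may be aimed at people who fail screening. Consent precedes the eligibility check (26a), and EQ-5D-5L, an inclusion criterion, is first scheduled at baseline (Table 2). The entry can also be read as reaching randomised participants, and nothing settles which is meant.
- *The steering committee removes people with knowledge of allocation.* Section 5d does not say that its rulings come after randomisation or take anyone out.
- *Section 18b promises collection after consent is withdrawn.* Its qualifier prevents that reading, although the boundary is left unstated.

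The planned best- and worst-case sensitivity analyses would also show how far missing outcomes could matter. They do not recover an outcome that was never sought.

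What survives is the contradiction in wording, the gap for ineligible randomised participants, and the effect that 11b could have on site conduct.

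**Conclusion.** Wrong as written: 11b contradicts 18b, 20a and 20c on whether participants who meet a discontinuation criterion remain in the trial, and no section clearly covers randomised participants later found ineligible. Applied literally by unblinded staff, 11b risks arm-dependent loss of week-15 outcomes.

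The documents do not allow the size of any bias to be derived. The +11% and +25% figures assume loss from the estimate, no benefit in non-attenders, no comparable loss among controls and, for the larger one, the full 20% dropout rate in the intervention arm as no-contact. They also relabel 0.74, which the plan uses as the effect for the whole trial, as the effect in attenders. The 0.01–0.20 SD range rests on assumed values as well. None of these figures measures what the rewording would gain, because some people will stay unreachable. The contradiction stands without them.

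**What to change.** Reconcile 11b with 18b and 20c:

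1. State in 11b that the listed events can end allocated treatment or sessions, but do not end follow-up or ITT membership. Replace the wording on exclusion from the study accordingly.
2. State that every randomised participant, including any later found ineligible, stays in the ITT set and is approached for the week-15 assessment, and for week 27 in the intervention arm. If the eligibility entry is meant only for people not yet randomised, say so.
3. State in 11b and 18b that, for an individual, only withdrawal of consent to data collection stops further collection, and that earlier data are kept as far as consent allows.

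The clinical criteria for stopping are left unchanged.

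The cost is a wording amendment, a matching line in the SAP and a site memo. The mailed and telephone assessments that may be needed are already provided for in sections 13 and 18b. The change can still protect data: 40 of 60 participants were enrolled by September 2025, so at that date 60 − 40 = 20 were still to come, and recruitment runs to March 2027. The article is based on protocol version 7 and version 10 is now in force, so the current wording should be checked first.
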